### Knowledge Translation

We will facilitate the dissemination of our research findings through publications (open access) and presentations at national and international congress meetings making scientific audiences aware of the findings and creating an interdisciplinary network that may influence both individual and public practice.

### Statistical Analysis Plan

The data will be analyzed by appropriate statistics. Student’s *t* test and Pearson correlation will be used for normally distributed variables. When necessary, log transformation will be used to normalize the data, or appropriate non-parametric tests will be employed (Mann–Whitney *U* test and Spearman rank correlation test). Adjusted multivariate analyses will be used to assess the differences and relationships between angiographic, laboratory, and clinical characteristics, stratifying the analysis on sex- and gender-related variables. Among the pre-specified subgroup analyses, we will explore the clinical presentation of ischemia (stable vs. acute coronary syndrome), the type of disease (obstructive vs. non-obstructive disease), traditional cardiovascular risk factors, medication adherence, and the gender construct including gender identity, gender role, gender relations, and institutionalized gender. We will consider the interaction term between sex and hormones in the changes of platelet biomarkers and angiographic index of coronary flow.

All calculations will be made using appropriate statistical software packages.

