## Abstract

Improvements in ischemic heart disease (IHD) management have been unbalanced between sexes, with coronary microvascular dysfunction considered the likely underlying reason. The Endocrine Vascular disease Approach (EVA) is an observational study (Clinicaltrial.gov NCT02737982) aiming to assess sex and gender interactions between coronary circulation, sexual hormones, and platelet function. Consecutive patients with IHD undergoing coronary angiography will be recruited: (1) to assess sex and gender differences in angiographic reperfusion indexes; (2) to evaluate the effects of estrogen/androgen on sex-related differences in myocardial ischemia; (3) to investigate the platelet biology differences between men and women with IHD; (4) to verify sex- and gender-driven interplay between response to percutaneous coronary intervention, platelets, sex hormones, and myocardial damage at baseline and its impact on 12-month outcomes. The integration of sex and gender in this translational project on IHD will contribute to the identification of new targets for further innovative clinical interventions.

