### Platelets: Evidence Suggesting Sex Differences Sheds Light on the Potential Role of Hormone Balance

Sex hormones operate at the cellular level, including vascular cells and activated cells recruited at the site of the athero-thombotic process, primarily platelets [58]. Sex differences in platelet reactivity have been reported in response to agonists, regardless of any ongoing anti-platelet therapy [59].

Ex vivo evidence showed that platelets from women without CAD are more reactive than those of men in response to standard concentrations of agonist [60–62], with a greater expression (50–80% higher compared to men) of glycoprotein (GP) IIb/IIIa receptors. Among patients, platelets from women, and in particular Caucasian women, bound more fibrinogen in response to low and high concentrations of ADP and showed more spontaneous aggregation compared to men after adjustment for multiple cardiovascular risk factors [63].

Mechanisms responsible for differences in platelet function are largely unknown. Estrogen and androgen receptors are expressed in platelets [58]; therefore, platelets are an excellent model for studying the non-genomic effects of hormones [64]. Specifically, human platelets have been shown to express only ER-beta and androgen receptors (AR). The effects of E2 and of other forms of estrogen, as well as those of testosterone, have been only partially explored and with conflicting results. Ex vivo acute treatment of platelets with estrone or estriol was shown to increase aggregation in response to common agonists [65]. Conversely, 3-month replacement therapy with estrogen induced a decrease in agonist-induced platelet aggregation in treated patients compared to control groups [66]. Accordingly, chronic treatment with high levels of E2 in experimental models (i.e., mice) produced a significant reduction in platelet responsiveness both ex vivo and in vivo, with a simultaneous increase of bleeding time and resistance to thromboembolism [67].

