#### Sample Size Calculation

Preliminary data reported a higher rate of pathologic post-procedural MBG in women (50%) compared to men (30%) despite a TIMI flow grade 3 after PCI [80].

Therefore, the study requires 186 patients (93 per group, ratio men/women 1:1) to detect a difference of 20% in MBG < 2 at baseline and after PCI between men and women, with an alpha error equal to 5% and a power of 80%. Considering a drop-out rate of around 10%, total sample size required is 210 (105 per group).

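### Student's t test is named with normality as its only condition, although equal group sizes are not secured; naming Welch's test would be a free, minor improvement

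*Protocol article*

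**What the plan says.** The Statistical Analysis Plan section of the protocol article states that Student's t "test and Pearson correlation will be used for normally distributed variables". The fallback is worded around distributional shape: "When necessary, log transformation will be used to normalize the data, or appropriate non-parametric tests will be employed", with Mann–Whitney and Spearman given as the alternatives. Unequal variances are not mentioned. The section then adds adjusted models ("Adjusted multivariate analyses will be used to assess the differences and relationships between angiographic, laboratory, and clinical characteristics") and lists subgroup analyses, among them stable versus acute presentation and "the type of disease (obstructive vs. non-obstructive disease").

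On group sizes, the Sample Size Calculation section plans 93 men and 93 women (105 each after drop-out). The stated purpose is "to detect a difference of 20% in MBG < 2 at baseline and after PCI between men and women", a binary endpoint, and the 5% alpha and 80% power are attached to it. The Abstract describes enrolment thus: "Consecutive patients with IHD undergoing coronary angiography will be recruited". No section gives a quota by sex or a target ratio for any subgroup.

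**The concern.** Student's t test pools the two sample variances. With equal group sizes, the pooled standard error agrees with the correct one even if the variances differ. With unequal sizes, pooling gives too much weight to the variance of the larger group. If the smaller group is the more variable, the standard error is too small and the test rejects too often. If the larger group is the more variable, the test is conservative and loses power.

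The comparisons concerned are those of continuous measurements: platelet markers, hormones and corrected TIMI frame counts. Platelet function in men and women is one of the four main objectives. As worded, a variable that looks normal but has different spreads in the two groups goes to the pooled test, because the fallback is triggered by non-normality and not by unequal variance.

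**Working it through.** **1. The plan's own figure.** Inputs from the Sample Size Calculation section: 50% in women, 30% in men, alpha 5% (taken as two-sided), power 80%, 1:1. The mean proportion is 0.40.

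n per group = [1.960 × √(2 × 0.40 × 0.60) + 0.8416 × √(0.50 × 0.50 + 0.30 × 0.70)]² / 0.20²
= [1.3579 + 0.5708]² / 0.04 = 93.0

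This reproduces 93 per group, 186 in total. Allowing for 10% drop-out, 186 / 0.9 = 206.7, i.e. 207, close to the stated 210. The calculation rests on two proportions, so the choice of t test does not enter it.

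**2. Type I error of the pooled test.** For group sizes n₁, n₂ and SDs s₁, s₂:

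- variance of the mean difference that the pooled test uses: Vp = [((n₁−1)s₁² + (n₂−1)s₂²)/(n₁+n₂−2)] × (1/n₁ + 1/n₂)
- true variance: Vt = s₁²/n₁ + s₂²/n₂
- large-sample type I error: 2 × [1 − Φ(1.96 × √(Vp/Vt))]

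The total of 186 comes from the protocol. The splits and SD ratios are assumptions.

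*62:124, smaller group more variable (SDs 1.5 and 1).* Pooled variance = (61 × 2.25 + 123 × 1)/184 = 1.414. Vp = 1.414 × 0.02419 = 0.03422. Vt = 2.25/62 + 1/124 = 0.04435. √(Vp/Vt) = 0.878. The effective critical value is 1.722, so the error is 8.5%.

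*62:124, larger group more variable (SDs 1 and 1.5).* Pooled variance = (61 × 1 + 123 × 2.25)/184 = 1.836. Vp = 0.04441. Vt = 1/62 + 2.25/124 = 0.03427. √(Vp/Vt) = 1.138. The effective critical value is 2.231, so the error is 2.6%.

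*93:93, SDs 1.5 and 1.* Vp = 1.625 × 2/93 = 0.03495. Vt = 3.25/93 = 0.03495. The two agree, so the error is 5.0%.

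**3. Simulation.** Normal data, equal means, two-sided 5%, 400,000 replicates per setting. Entries for the pooled test are for SD ratios 1.25 / 1.5 / 2.

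| Split | Pooled test, smaller group more variable | Pooled test, larger group more variable | Welch, all settings in the row |
|---|---|---|---|
| 80:106 | 5.7 / 6.4 / 7.3% | 4.3 / 3.8 / 3.4% | 4.9–5.1% |
| 62:124 | 6.9 / 8.5 / 11.1% | 3.5 / 2.6 / 1.7% | 5.0–5.1% |
| 47:139 | 8.0 / 10.6 / 14.9% | 2.9 / 1.8 / 0.8% | 5.0–5.1% |

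At 93:93 the pooled test stays between 5.0% and 5.1% for the same three ratios. With equal SDs it holds 5% at every split. The level is disturbed only when sizes and spreads differ together.

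**4. Price of Welch's test.** With equal SDs, a 62:124 split and a standardised difference of 0.45, simulated power was 81.9% for the pooled test and 81.6% for Welch's, a loss of 0.3 points.

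**The case against.** Much of the case on the other side stands.

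- **Balance is planned.** The article plans 1:1 and, among the main objectives, describes the platelet comparison as one between men and women matched by age and clinical characteristics. If 1:1 is achieved, Student's t test is safe. The splits above are not forecasts, and the text does not expressly assign a t test to the subgroup analyses.
- **The 5% belongs elsewhere.** A reader might infer that the stated 5% error is wrong. The only stated 5% belongs to the MBG comparison, which no t test analyses. Nor is any confidence interval method stated, so the most that can be said is that an interval built from the pooled standard error would share the fault.
- **No SDs are given.** A reader might also take the Rationale's report of "greater expression (50–80% higher compared to men") and, assuming a constant coefficient of variation, conclude that SDs in women are 1.5 to 1.8 times larger. The documents do not support this. The figure is a difference in level for one receptor, in women without coronary artery disease, and says nothing about spread in this cohort. The step also defeats itself: under a constant coefficient of variation equal means imply equal SDs, so at the null the pooled test would hold its level.
- **The fallbacks help in part.** Log transformation tends to equalise spreads that grow with the mean. Its stated trigger is normality, however, so it is not sure to be used where spread is the only problem.
- **Level of detail.** Pooled versus Welch is often settled in a full analysis plan, and authors sometimes write Student's t loosely. That lowers the weight of the point. It does not remove it, because the article names a specific test and a specific condition for it.

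**Conclusion.** The point holds as a minor one. The named test keeps its level under unequal variances only if group sizes are close to equal, and nothing in the article secures that for men versus women or for the subgroups. If sizes and spreads both differ, the error can move either way, by an amount that depends on values the documents do not give. The 8.5% and 2.6% at 1:2 with an SD ratio of 1.5 show the order of the effect under assumed values. They do not show that any EVA result will be wrong, and the direction cannot be predicted. The primary sample-size reasoning is sound on this score and needs no change.

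**What to change.** In the Statistical Analysis Plan section, replace Student's t test by Welch's unequal-variance t test for independent two-group comparisons of normally distributed or log-transformed variables. If Welch's test was meant all along, saying so settles the matter.

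The cost is one line of wording. No patients, data or change to the 186 or 210 are needed. The power loss when variances are in fact equal is about 0.3 points at a 1:2 split.

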### EVA Research Hypothesis and Aims

The research hypothesis is that women with IHD have a higher proportion of CMD due to a higher release of platelet-derived vasoconstrictor molecules such as thromboxanes, despite anti-platelet therapy. This status of hyper-activation might be modulated differentially by sex hormone balance among sexes according to age (Fig. 1). Further evidence on platelet biology and sex hormone interplay will provide mechanistic insights to understand CMD. Platelet activation markers will potentially be used as breakthrough innovative biomarkers to better predict outcomes of IHD patients.

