**Fig. 1 Fig1:**
[figure not shown]
The EVA hypothesis: platelets, coronary microvascular dysfunction, and unbalanced clinical outcomes in women and men with ischemic heart disease

We plan to conduct an observational study on patients affected by IHD undergoing angiography and/or PCI. Main objectives of EVA are:To assess the sex–gender differences in severity of microvascular reperfusion damage in patients with IHD;To evaluate estrogen/androgen effects on sex-related differences in myocardial ischemia–reperfusion damage occurring during PCI;To investigate the differences in terms of platelet function between men and women affected by IHD and matched by age and clinical characteristics, according to CMD and CAD type;To verify sex- and gender-driven interplay between the response to PCI procedure, platelet function, sex hormones, reperfusion imaging, and myocardial damage severity at baseline and its impact on outcomes at 12-month follow-up.

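### Read literally, stratifying the adjusted models by sex yields no adjusted sex difference in MBG < 2, cTFC or 12-month outcomes, and no test of most differences in association by sex

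*Protocol article*

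**What the plan says.** The Statistical Analysis Plan section of the protocol article gives the adjusted analyses one sentence. Their purpose: "Adjusted multivariate analyses will be used to assess the differences and relationships between angiographic, laboratory, and clinical characteristics". Their method: "stratifying the analysis on sex- and gender-related variables".

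Two other sentences in that section bear on sex:

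- Simple two-group and correlation methods: "Student’s *t* test and Pearson correlation will be used for normally distributed variables", with rank-based alternatives.
- One product term: "We will consider the interaction term between sex and hormones in the changes of platelet biomarkers and angiographic index of coronary flow".

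The target is a contrast between the sexes. The Abstract puts first the aim "to assess sex and gender differences in angiographic reperfusion indexes", and the first main objective under EVA Research Hypothesis and Aims is "To assess the sex–gender differences in severity of microvascular reperfusion damage in patients with IHD". The Sample Size Calculation section powers a men-versus-women difference of 20 percentage points in MBG < 2.

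**The concern.** If sex defines the strata, each model is fitted to women only or men only. Sex is then constant within every model and has no coefficient. Such models show how age, hormones or platelet markers relate to blush grade within each sex. They do not show how much more often women have MBG < 2 than men of the same age and presentation, which is what the first objective asks.

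This matters because the study is an observational cohort. Study Design and Population admits stable disease, non-ST-elevation acute coronary syndrome and ST-elevation infarction. If women and men differ in age or in this mix, the crude contrast carries those differences, and adjustment would be the remedy.

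A second consequence concerns effect modification. Two separately fitted models do not by themselves test whether an association differs between the sexes. Without a product term, the reader is left to compare two sets of estimates.

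**Working it through.** **1. The plan's own figure.** Inputs from Sample Size Calculation: 50% in women, 30% in men, alpha 5%, power 80%. Sidedness is not stated; two-sided reproduces the figure. With pooled variance under the null and no continuity correction:

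n per group = [1.95996 × √(2 × 0.4 × 0.6) + 0.84162 × √(0.5 × 0.5 + 0.3 × 0.7)]² / 0.20²
= (1.3579 + 0.5708)² / 0.04 = 3.720 / 0.04 ≈ 93.

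The stated 93 per group is reproduced. Power is 80.0% at 93 and 84.6% at 105 per group. The study is therefore sized for a direct, unadjusted comparison of two proportions. No figure in the plan is wrong; the problem lies in how the adjusted analysis is worded.

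**2. What each planned analysis can deliver.**

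| Analysis in the plan | Sex difference in MBG < 2 or cTFC | Sex difference in 12-month outcomes | Test that an association differs by sex |
|---|---|---|---|
| Unadjusted men-versus-women comparison | Yes, unadjusted | Yes, unadjusted | No |
| Adjusted models within sex strata | No | No | No |
| Sex-by-hormones interaction | Only conditional on hormone level | Not covered | Hormones only |

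So under the literal reading, no analysis gives a confounder-adjusted overall sex effect on the main angiographic endpoint. Sex-by-platelet and sex-by-gender questions have no product term, although the fourth objective asks about the interplay of sex and gender with platelets, hormones and outcomes.

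**3. Comparing strata (illustration only).** Assumptions, not taken from the article: an association that is identical in both sexes, equal halves, and 80% power in the whole cohort.

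- Standardised effect in the whole cohort: 1.960 + 0.842 = 2.802.
- Power within one sex: Φ(2.802/√2 − 1.960) = Φ(0.021) = 0.508.
- Chance that exactly one sex is significant: 2 × 0.508 × 0.492 = 0.50.
- Range: with within-sex power of 30%, 50% or 80%, that chance is 2 × 0.3 × 0.7 = 0.42, 2 × 0.5 × 0.5 = 0.50, or 2 × 0.8 × 0.2 = 0.32.

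**4. Precision of a formal interaction.** With equal halves, the difference between the two within-sex estimates has twice the standard error of the common estimate. For an interaction as large as the effect in step 3, power is Φ(2.802/2 − 1.960) = Φ(−0.559) = 0.288, about 29%.

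**5. Room for adjustment.** At the planned rates, 93 × 0.5 + 93 × 0.3 = 46.5 + 27.9 ≈ 74 patients would have MBG < 2. That supports a moderate set of confounders, but not many product terms at once.

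**The case against.** The strongest reply has five parts.

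- **The sex contrast is still in the study.** A reader might infer from the stratification that it has been removed. The documents do not support that: the sample size is built on a direct comparison of men and women, and two-group tests are listed. This stands in full. What is lacking is the adjusted contrast.
- **A model on both sexes is already planned.** The sex-by-hormones term can only be fitted to men and women together. Because the rationale describes both cTFC and MBG as angiographic indexes of coronary flow, that model may include MBG. This stands in part. Its sex coefficient is conditional on hormone level, and hormones are a hypothesised intermediate, so it is not the overall adjusted sex effect. It also does not reach clinical outcomes.
- **The third objective matches men and women on age and clinical features.** That addresses confounding for the platelet comparison. It is not stated for MBG or for 12-month outcomes.
- **The wording is ambiguous.** Stratifying may be loose language for analysis by sex and gender, and strata formed on gender variables alone would leave sex estimable within them. The same sentence also gives the assessment of differences as a purpose. This is fair, and is why the point is tied to the literal reading. But the section names a product term for one question and stratification for the rest, so the two are not clearly the same thing.
- **The article condenses a fuller plan.** Covariate lists and a formal pathway analysis may properly sit there. A reader might take the stated hypothesis, "women with IHD have a higher proportion of CMD due to a higher release of platelet-derived vasoconstrictor molecules", to require a mediation analysis in this text. Its absence from an article is not a fault, and none is asked for here. The stratification is different, because it is stated in the article.

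A reader might also infer that the investigators will declare a sex difference when a result is significant in one sex only. The plan states no such rule, so the 50% figure illustrates a general hazard and does not measure an error in this plan.

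**Conclusion.** The point holds in a limited form. As worded, the adjusted analyses give no adjusted sex difference in MBG < 2, cTFC or 12-month outcomes, and they leave differences in association by sex untested except for hormones. The remaining direct estimate of the sex difference is sound in size but unadjusted, in a cohort that mixes acute and stable presentations.

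This rests on reading the stratification as separate models for women and men. How far confounding would move the crude contrast, and in which direction, cannot be worked out from the article, which gives no age or presentation mix by sex. The sample size is unaffected. The change is worth making before analysis because it answers the study's own first question with less risk of bias.

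**What to change.** Reword the adjusted-analysis sentence to say three things:

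1. For MBG < 2 and the other main endpoints, including 12-month outcomes, fit one model on all patients with sex as the exposure and the collected confounders (for example age, clinical presentation, CAD type and risk factors). Leave hormone and platelet terms out of this model because they are hypothesised intermediates.
2. Assess effect modification in separate pooled models with product terms of sex with hormone, platelet marker or gender variable. Report each as an estimate with a confidence interval.
3. Keep sex-stratified results as descriptive.

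The cost is wording and some extra analysis work, with no new data and no more patients. The downside is imprecise interaction estimates, so the text should say that a wide interval is not evidence that the sexes are alike.

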#### Sample Size Calculation

Preliminary data reported a higher rate of pathologic post-procedural MBG in women (50%) compared to men (30%) despite a TIMI flow grade 3 after PCI [80].

Therefore, the study requires 186 patients (93 per group, ratio men/women 1:1) to detect a difference of 20% in MBG < 2 at baseline and after PCI between men and women, with an alpha error equal to 5% and a power of 80%. Considering a drop-out rate of around 10%, total sample size required is 210 (105 per group).

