**Table 1 Tab1:**
[figure not shown]
EVA Study design

A registry will be built up of men and women aged 18 and older with suspected IHD who were referred to the catheterization laboratory in order to undergo coronary angiography and/or PCI. Patients will be recruited according to the eligibility criteria reported in Table 2. Therefore, the EVA study population will include patients with stable CAD, patients with non-ST elevation (NSTE) ACS, and patients with ST elevation myocardial infarction (STEMI).

**Table 2 Tab2:** EVA study population eligibility criteria

Inclusion criteria	Exclusion criteria
▪ Patients with ischemic heart disease (acute or chronic) undergoing percutaneous coronary intervention (urgent or elective) ▪ Written informed consent ▪ Both sexes ▪ Aged more than 18 years	▪ Life expectancy less than 12 months ▪ Active cancer (i.e., chemotherapy or ≤ 5 years from diagnosis) ▪ Pregnancy ▪ Previous coronary artery bypass graft ▪ Documented moderate–severe valvular heart disease ▪ Biological or mechanical valves

The study will be conducted in full conformance with the principles of the Declaration of Helsinki, the laws and regulations of Italy, or whichever affords the greater protection to the individual. The study has obtained the required authorization by the local Ethics Committee of Policlinico Umberto I, Sapienza University of Rome (reference 3786, 24/09/2015). Written informed consent will be obtained from all patients.

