Among the study population, we will select (1) patients undergoing urgent PCI, specifically subjects who presented within 12 h of the onset of chest pain, who had ST segment elevation of more than 0.1 mV in two contiguous leads, and for whom the clinical decision was made to treat with PCI (STEMI); (2) patients with NSTE ACS defined by acute chest pain but no persistent ST segment elevation. ECG changes may include transient ST segment elevation, persistent or transient ST segment depression, T-wave inversion, flat T waves, or pseudo-normalization of T waves or the ECG may be normal. Myocardial ischemia can occur with (myocardial infarction–NSTEMI) or without cell loss (unstable angina); (3) patients undergoing coronary angiography and elective PCI for stable angina, with stress test inducible myocardial ischemia and de novo native coronary lesion with a stenosis of less 50% (no obstructive CAD) or > 50% stenosis in any epicardial artery (mono-vessel obstructive CAD). Patients will be treated according to standard guidelines based on the CAD type, either with PCI or coronary artery bypass graft.

The recruitment phase started in April 2016 and, currently, 200 patients have already been included in the study.

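### The 93 per sex is sized on post-PCI blush grade, but the text also enrols patients who will have no post-PCI reading, so the stated 80% power is not assured

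*Protocol article*

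**What the plan says.** All references are to the protocol article.

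- **Sample Size Calculation, planning rates.** Preliminary data showed a "higher rate of pathologic post-procedural MBG in women (50%) compared to men (30%) despite a TIMI flow grade 3 after PCI".
- **Sample Size Calculation, target.** It concludes that "the study requires 186 patients (93 per group, ratio men/women 1:1) to detect a difference of 20% in MBG < 2". The comparison is described as "MBG < 2 at baseline and after PCI between men and women", so one number serves two time points.
- **Sample Size Calculation, inflation.** "Considering a drop-out rate of around 10%, total sample size required is 210 (105 per group"). No other allowance is made.
- **Study Design and Population, Table 2.** Undergoing PCI, urgent or elective, is an inclusion criterion.
- **Study Design and Population, text.** The registry takes patients "referred to the catheterization laboratory in order to undergo coronary angiography and/or PCI". The third selected group includes stable patients with a stenosis below 50%. The section adds: "Patients will be treated according to standard guidelines based on the CAD type, either with PCI or coronary artery bypass graft".
- **Other sections that use patients without PCI.** EVA Research Hypothesis and Aims describes patients having angiography and/or PCI. The angiographic definitions of CAD include a non-obstructive class (INOCA). The CMR Sub-Study draws 10 patients whose angiography showed no obstructive disease. The Statistical Analysis Plan section pre-specifies obstructive versus non-obstructive subgroups.
- **Corrected TIMI Frame Count and Myocardial Blush Grade.** Impairment is an MBG below 2, either at rest or after PCI.

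**The concern.** A sample size holds for the patients in whom the sizing endpoint can be measured. Here that endpoint is MBG after PCI. A patient who has angiography only, or who goes to bypass surgery, has no such reading. If such patients count toward the 105 per sex, the number available for the post-PCI comparison falls below 105, and the plan makes no allowance for this.

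Two features make it worse. First, the same 93 is applied to baseline MBG without a baseline rate, so the power of that comparison is unsupported. Second, the definition of impairment accepts either a resting or a post-PCI reading. That leaves room to fill the gap with resting values, which would combine two measurements in one comparison when a planning rate exists for only one of them.

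At stake is whether a null result on sex differences in post-PCI MBG could be read as coming from a study with 80% power.

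**Working it through.** **Inputs from the Sample Size Calculation:** p1 = 0.50 (women), p2 = 0.30 (men), alpha 5%, power 80%, ratio 1:1, drop-out about 10%, 105 per sex enrolled. The text does not say whether the test is two-sided; two-sided reproduces the stated figure.

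**Step 1. Reproduce 93.** Two-proportion test, pooled variance under the null, no continuity correction, mean rate 0.40:

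n = [1.960 × √(2 × 0.40 × 0.60) + 0.842 × √(0.50 × 0.50 + 0.30 × 0.70)]² / 0.20²

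= [1.358 + 0.571]² / 0.04 = 93.0 per sex.

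Power at 93 per sex is 0.800. The stated number is right for its inputs.

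**Step 2. Reproduce 210.** 186 / 0.9 = 206.7, so 207; per sex 93 / 0.9 = 103.3, so 104, or 208 in total. The stated 210 is consistent with a loss of around 10%.

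**Step 3. How many patients without PCI can be absorbed?**

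- If drop-out costs no MBG reading: (105 − 93) / 105 = 11.4% per sex.
- If drop-out costs the full 10%: 105 × 0.9 = 94.5 remain, and (94.5 − 93) / 94.5 = 1.6% per sex.

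**Step 4. Power of the post-PCI comparison beyond that.** With n evaluable per sex, power = Φ[(0.20 × √n − 1.358) / 0.678]. The share without PCI, f, is an assumption, taken as equal in both sexes.

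| f | n, no other loss: 105(1 − f) | Power | n, with 10% loss: 94.5(1 − f) | Power |
|---|---|---|---|---|
| 0% | 105 | 0.85 | 94.5 | 0.81 |
| 10% | 94.5 | 0.81 | 85.0 | 0.76 |
| 20% | 84 | 0.76 | 75.6 | 0.71 |
| 30% | 73.5 | 0.70 | 66.1 | 0.65 |

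The two power columns are alternatives that depend on what drop-out means.

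**Step 5. What if resting MBG fills the gap?** Suppose, as an illustration only, that resting MBG is impaired in 30% of both sexes. The pooled rate in women becomes 0.50(1 − f) + 0.30f, while men stay at 0.30. With 93 per sex analysed, f = 10% gives 0.48 versus 0.30 and power 0.71; f = 20% gives 0.46 versus 0.30 and power 0.61. Pooling therefore need not restore the power, and it changes what is being compared.

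**The case against.** The strongest reply is Table 2. PCI is a formal inclusion criterion there, and the registry paragraph itself refers to Table 2 for eligibility. If Table 2 governs, every enrolled patient has PCI and the stated power stands. This is a real point, and it rules out saying as fact that the 210 contains patients without PCI. It does not settle the matter, because the selection text, the INOCA class, the non-obstructive arm of the CMR Sub-Study and the obstructive versus non-obstructive subgroup analysis all use patients for whom angiography without PCI is expected.

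A reader might go further and infer that the 80% power is definitely missed. The documents do not support that: they give no share without PCI, and about 11% per sex is absorbed if drop-out costs no readings.

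A reader might also infer that the loss falls mainly on women. The rationale discusses microvascular dysfunction in women as a mechanism, particularly in INOCA. It does not say that women in this cohort will have PCI less often, so equal shares are used above.

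Nor can it be said that the drop-out allowance covers the wrong loss altogether. Loss during the 12-month follow-up would not remove a reading taken at the index procedure. However, the Data Collection, Management, and Quality Assurance section excludes patients with unresolved discrepant data, which could. Hence both versions are shown.

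Finally, baseline MBG can be read without PCI, and nothing says that resting values will replace missing post-PCI ones. That limits the shortfall to the post-PCI comparison and makes pooling a risk left open rather than a stated plan. The baseline comparison still has no planning rate.

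**Conclusion.** The arithmetic is correct; the mismatch lies in the population to which it is applied. The 93 per sex is valid for patients with a readable post-PCI MBG, while the article's own descriptions of who is enrolled conflict on whether all patients have PCI. The 80% power for the post-PCI comparison is therefore not assured.

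The size depends on an unknown share without PCI: no shortfall up to about 11% per sex if nothing else is lost, power of about 0.76 at 20% and 0.70 at 30%, or about 0.71 and 0.65 if the 10% drop-out also removes readings. These figures rest on the planning rates of 50% and 30%, a two-sided 5% test and equal shares in both sexes.

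This is worth correcting, but it does not undermine the study. It is also more than a detail that an article leaves to a fuller document, because the article states the calculation and the conflicting population itself.

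**What to change.** 1. Reconcile Table 2 with the registry and selection text in Study Design and Population, so that it is clear whether patients without PCI count toward the 210.
2. State that the 93 per sex are PCI-treated patients with a readable post-PCI MBG.
3. Study Design and Population reports 200 patients already included. Count those with a readable post-PCI MBG by sex, and restate the power of the post-PCI comparison for the evaluable number.
4. Analyse resting MBG in patients without PCI separately and keep it out of the powered comparison. Do not attach the 80% to baseline MBG unless a baseline rate is given.

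The cost is rewording, one count from existing data and possibly a less favourable stated power. No new patients or procedures are needed.
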